### 3.6. Randomization, allocation concealment, and blinding

Randomization is performed the day before surgery using the CleanWeb web-based system (Telemedicine Technologies, France). A computer-generated permuted-block randomization list with varying block sizes (ratio 1:1) was implemented on the website at the beginning of the study by an independent data manager. The block size is unknown to the investigators. When written informed consent was obtained, the investigator entered data online regarding each patient to enable inclusion and randomization. The treatment randomly allocated to the patient is immediately provided to the investigator by the website.

Patients and outcome assessors (neurosurgeons) are blinded to the treatment allocated.

### 3.7. Study procedure and interventions

In the interventional group, patients receive hypertonic sodium lactate infusion for brain relaxation. The intravenous infusion of hypertonic sodium lactate (Na^+^ 1000 mmol/L, lactate 1000 mmol/L, prepared by the Etablissement Pharmaceutique Hopitaux de Paris, Assistance Publique Hopitaux de Paris, Paris) is started at the time of skin incision and is administered over 15 to 20 minutes at 2.5 mL/kg (maximal dose of 250 mL; patients whose weight is > 100 kg are excluded).

In the conventional group, patients receive an equimolar dose of 20% mannitol infusion for brain relaxation. The intravenous infusion of 20% mannitol is started at the time of skin incision and is administered over 15 to 20 minutes at 5 mL/kg (1 g/kg) (maximal dose of 500 mL; patients whose weight is > 100 kg are excluded). Seo et al reported that 1 g/kg was the optimal dose of mannitol for intraoperative brain relaxation in patients undergoing craniotomy for supratentorial brain tumor resection.^[8]^

If a greater degree of brain relaxation is required during surgery, a rescue therapy is administered according to the following stepwise strategy: (1) administration of additional mannitol 0.25 g/kg; (2) deepening anesthesia to achieve a BIS value between 20 and 40; and (3) administration of an intravenous bolus of sodium thiopental 5 mg/kg.

### 3.8. Outcome measures

The primary outcome is the proportion of satisfactory brain relaxation, defined as brain relaxation score of 3 or 4. Brain relaxation is assessed immediately after opening the dura by the neurosurgeon in charge of the patient blinded to the treatment allocated. The assessment of brain relaxation is performed using a validated 4-point scale,^[21]^ with: 1 = bulging brain; 2 = firm brain; 3 = satisfactorily relaxed; and 4 = perfectly relaxed).

Secondary outcomes are proportion of patients requiring a rescue therapy to improve the degree of brain relaxation during surgery; blood pH, serum osmolality, natremia, kaliemia, and lactatemia at baseline (before skin incision), and at 30 minutes, 60 minutes, 180 minutes, 24 hours, and 48 hours after the end of osmotherapy (either mannitol or hypertonic sodium lactate); serum levels of S100B and NSE proteins at baseline and at 24 hours and 48 hours after the end of osmotherapy; postoperative recovery assessed by the Glasgow Coma Scale on day 1 and on day 2 after surgery and by the Karnofsky performance status on day 30 after surgery; cognitive performance at baseline (the day before surgery) and on day 2 after surgery; volume of postoperative brain edema assessed on brain MRI performed on day 2 after surgery; and postoperative morbidity and mortality on day 30 after surgery.

Cognitive performance is assessed the day before surgery and on day 2 after surgery using a battery of validated neuropsychological tests during a 20-min face-to-face interview with an investigator who was specifically trained by a neuropsychologist (GC) prior the start of the study. Seven neuropsychological tests are performed to explore 5 different cognitive domains: (a) attention, using the Trail Making Test, part A; (b) executive function, using the Trail Making Test, part B and the semantic-phonemic switching verbal fluency test; (c) verbal fluency, using the Isaacs Set Test and the semantic-phonemic clustering verbal fluency test; (d) learning and episodic verbal memory, using the Memory Impairment Screen test; and (e) verbal short term and working memory, using the forward and reverse digit span memory test.

Postoperative morbidity includes cardiac arrythmia that occurs within 2 days after surgery, any complication requiring surgical revision, unexpected cerebral edema, intracranial hypertension, intracerebral hematoma, stroke, seizure, coma, readmission in the intensive care unit or in the hospital, surgical wound infection, or pneumonia.

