### 3.5. Study outline

Eligible patients are screened and informed during the anesthesia consultation. Written informed consent is obtained the day before surgery by investigators after oral explanation of the study. After written informed consent is obtained, patients are randomized using a computer-generated randomization list implemented on the CleanWeb web-based system (Telemedicine Technologies, France).

After randomization, a first cognitive assessment using a battery of validated neuropsychological tests (see below) is performed by an investigator who was specifically trained by a neuropsychologist (GC) prior to the start of the study. Patient characteristics, past medical history including ASA physical status, type of brain tumor, preoperative management of brain tumor (corticosteroid therapy, antiepileptic therapy, chemotherapy, and/or radiotherapy), preoperative Karnosky performance status, and preoperative neurological status including Glasgow Coma Scale are collected. Midline shift, brain tumor size, and localization, and the size of peritumoral edema are extracted from the preoperative brain imaging [either brain magnetic resonance imaging (MRI) or computed tomography scan]. Included patients undergo a first cognitive assessment using a battery of validated neuropsychological tests (see below).

On arrival in the operating room, standard monitoring (General Electric Healthcare) is put in place. A peripheral venous catheter dedicated to anesthetic drug infusion is inserted in a forearm vein. All patients receive intravenous anesthesia based on manually driven target-controlled infusion of propofol and remifentanil aiming to maintain bispectral index (BIS) values between 40 and 60. All patients are paralyzed using nondepolarizing neuromuscular blocking agent (either cisatracurium or atracurium).

After induction of anesthesia, patients are intubated, and tidal volume and respiratory rate are set to maintain the end-tidal carbon dioxide between 35 and 40 mm Hg. Inspired oxygen fraction is adjusted to obtain a pulse oximetry ≥ 95%. A second peripheral venous catheter, a urinary catheter, and an indwelling arterial catheter introduced in a radial artery are implemented.

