The treatment allocated by randomization for brain relaxation, that is, mannitol (conventional group) or hypertonic sodium lactate (intervention group) infusion, is started at the time of skin incision and is administered over 15 to 20 minutes (see below). The degree of brain relaxation (primary outcome) is assessed by the neurosurgeon immediately after opening the dura. If a greater degree of brain relaxation is required, a rescue therapy is administered according to the following stepwise strategy: (1) administration of additional mannitol 0.25 g/kg; (2) deepening anesthesia to achieve a BIS value between 20 and 40; and (3) administration of an intravenous bolus of sodium thiopental 5 mg/kg.

Blood samples are collected immediately before skin incision (baseline, T_0_), and at 30 minutes, 60 minutes, 180 minutes, 24 hours, and 48 hours after the end of osmotherapy (either mannitol or hypertonic sodium lactate) to measure blood pH, natremia, kaliemia, lactatemia, and serum osmolality. Serum levels of S100B protein and neuron-specific enolase (NSE) are measured at baseline, and at 24 hours and 48 hours after the end of osmotherapy.

The following surgical and anesthetic details are recorded: type and duration of surgery; intraoperative blood loss and urine output, blood transfusion and total volume of fluids infused; type and total dose of drugs administered; and all blood pressure, heart rate, pulse oximetry, and end-tidal carbon dioxide values from induction of anesthesia to discharge from the operating room.

At the end of surgery, patients are admitted to the postoperative surgical intensive care unit during at least the first postoperative 24 hours. Postoperative neurological status (Glasgow Coma Scale, new transient, or permanent neurological deficits), urine output, blood transfusion, and total volume of fluids infused are assessed on days 1 and 2 after surgery. Brain MRI is performed within the first 2 days after surgery to quantify postoperative brain edema and ischemic changes, and postoperative midline shift.

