### 3.11. Sample size calculation

No previous study has assessed the clinical effectiveness of hypertonic sodium lactate infusion for intraoperative brain relaxation in patients undergoing scheduled craniotomy for supratentorial brain tumor resection. Thus, no assumption can be made on the expected difference in primary outcome between groups. The sample size calculation was based on the expected measurement accuracy of the primary outcome in the interventional group.

Seo et al reported a satisfactory brain relaxation (primary outcome) in 65% of patients who received the same dose of 20% mannitol as in the conventional group.^[8]^ We hypothesized that the primary outcome will be at least 55% in the interventional group to consider that hypertonic lactate sodium infusion provides a clinically relevant brain relaxation for supratentorial brain tumor resection.

A sample size of 25 patients was calculated to achieve a measurement accuracy of the primary outcome of 20% in the interventional group. In this phase II pilot study, 2 groups of patients are included to check whether the expected rate of the primary outcome is the same in the conventional group as in the study from Seo et al^[8]^ and to provide reliable data for further studies. Thus, the inclusion of a total sample size of 50 patients (25 patients per group) is planned.

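### The edema outcome is a postoperative MRI volume with no like-for-like preoperative measure, so precision is lost and chance imbalance cannot be cleanly corrected

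*Protocol article*

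**What the plan says.** Section 3.8 (Outcome measures) defines the edema outcome as the "volume of postoperative brain edema assessed on brain MRI performed on day 2 after surgery". It is an absolute postoperative quantity from one modality. Section 3.5 (Study outline) describes the purpose of that scan in similar terms, with slightly different timing: "Brain MRI is performed within the first 2 days after surgery to quantify postoperative brain edema and ischemic changes, and postoperative midline shift".

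The preoperative record is described only in section 3.5: "the size of peritumoral edema are extracted from the preoperative brain imaging [either brain magnetic resonance imaging (MRI) or computed tomography scan". The metric behind the word *size* is not given, and two modalities are allowed.

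Other secondary outcomes in section 3.8 do carry a named baseline. Cognition is one: "cognitive performance at baseline (the day before surgery) and on day 2 after surgery". Blood chemistry and the S100B and NSE proteins are also listed with a baseline value. Edema volume is not.

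On allocation, section 3.6 states "A computer-generated permuted-block randomization list with varying block sizes (ratio 1:1") and mentions no stratification by edema. Section 3.11 gives the size: "the inclusion of a total sample size of 50 patients (25 patients per group) is planned". Section 3.12 (Statistical analysis) compares quantitative variables by Mann–Whitney or Student *t* test, on an intention-to-treat basis at the 0.05 level, and names no baseline covariate.

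**The concern.** The introduction of the article describes peritumoral edema as already present before surgery and as a cause of raised intracranial pressure. If part of it is still visible on the early postoperative scan, the postoperative volume mixes what the patient brought to the operation with what followed it.

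The first part is variation between patients that has nothing to do with the allocated infusion. A baseline on the same scale would let the analysis remove much of it. As written, baseline and outcome are described in different terms and possibly come from different modalities, so a usable baseline volume is not assured.

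Three things are at stake:
- The sensitivity of this comparison.
- The ability to correct a chance difference in preoperative edema between two small groups.
- The usefulness of the pilot as a source of design figures. A later trial of this outcome would need the SD given baseline, or the pre/post correlation, and a size from mixed modalities cannot supply either reliably.

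**Working it through.** **Inputs from the protocol article.** 25 per group (section 3.11); significance level 0.05 (section 3.12), taken as two-sided because the side is not stated; 1:1 allocation without stated stratification (section 3.6).

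**Assumed, because the documents give no figure.** Pre/post correlation r of edema volume, mainly 0.6 to 0.8, with 0.3 as a low value. Reliability of a mismatched baseline, 0.4 to 0.6. Power of 80%, used only as a yardstick.

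**1. The plan's own figure.** The 25 comes from the precision of the primary proportion: "A sample size of 25 patients was calculated to achieve a measurement accuracy of the primary outcome of 20% in the interventional group". Read as a 95% half-width of 20 points, n = 1.96² × p(1 − p) / 0.20².
- p = 0.50: 24.01, rounded up to 25.
- p = 0.55, the stated hypothesis: 23.8, rounded up to 24.

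The figure reproduces. Nothing below changes it.

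**2. Is the unadjusted comparison biased?** 20,000 trials with no treatment effect were simulated. Each had 25 per group, a log-normal baseline edema (log mean 3, log SD 0.8), and postoperative edema equal to 0.7 × baseline plus an independent log-normal term (log mean 2, log SD 0.8). The Mann–Whitney test rejected in 4.8% of trials. The mean group difference was −0.04 with a simulation standard error of 0.04. No bias and no inflated error rate were seen.

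**3. Chance imbalance in preoperative edema.** Standard error of the baseline difference = √(2/25) = 0.28 SD.
- Beyond 0.25 SD in either direction: z = 0.25/0.283 = 0.88, probability 37.7%.
- Beyond 0.5 SD: z = 0.5/0.283 = 1.77, probability 7.7%.

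An imbalance of 0.5 SD carries r × 0.5 = 0.3 to 0.4 SD into the postoperative comparison for r of 0.6 to 0.8.

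**4. Detectable difference.** A two-sample *t* test with 25 per group gives 0.81 SD (normal approximation: (1.960 + 0.842) × 0.283 = 0.79). Covariate adjustment multiplies this by √(1 − r²). A baseline of reliability k multiplies it by √(1 − r²k). A change score, with equal variances before and after, multiplies it by √(2(1 − r)).

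| Analysis | r = 0.3 | r = 0.6 | r = 0.8 |
|---|---|---|---|
| Postoperative volume, unadjusted | 0.81 | 0.81 | 0.81 |
| Adjusted for like-for-like volume | 0.77 | 0.65 | 0.49 |
| Change score | 0.96 | 0.72 | 0.51 |

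With a mismatched baseline as covariate, the result is 0.75 SD at r = 0.6, k = 0.4 and 0.63 SD at r = 0.8, k = 0.6.

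Adjustment for a comparable baseline removes r² of the variance: 9%, 36% and 64% at the three correlations. The change score never beats adjustment, and below r = 0.5 it is worse than the present unadjusted outcome.

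**The case against.** A reader might infer that edema due to treatment cannot be separated from edema already there. For the group comparison the documents do not support that. Allocation is randomized with a concurrent mannitol group, so preoperative edema is balanced in expectation, and the ordinary test and confidence interval already allow for chance imbalance. Step 2 agrees. The statement is fair only within one patient: on the measures as described, new edema cannot be told from residual edema.

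A reader might also infer that no usable baseline can exist. That goes too far as well. The protocol draws preoperative data from a scan, so a volume can be measured on it, and even the recorded size could serve as a weaker covariate.

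Three further objections carry weight. First, this is a condensed article: *size* may be defined as a volume in the full protocol, and adjustment may be specified in the analysis plan. That would shrink the point, but the article would still allow CT for one measurement and specify MRI for the other. Second, the article's key points say that the study is not designed to compare the groups with adequate power. The detectable differences therefore measure relative precision and do not show that the trial fails an aim. The same key points promise high-quality data for designing further studies, and a comparable baseline serves that aim. Third, the correlations are assumed, and at 0.3 there is little to gain.

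**Conclusion.** The point holds as one of precision and measurement consistency in one secondary outcome. The article sets an unadjusted postoperative MRI volume against a preoperative size from MRI or CT, and it assures no like-for-like baseline. The comparison stays unbiased, and the sample size and primary outcome are unaffected.

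The loss is the gap between about 0.81 SD and 0.65 to 0.49 SD in detectable difference, if the pre/post correlation is 0.6 to 0.8. It nearly vanishes at 0.3. The standard error of 0.28 SD for the baseline difference needs only the 25 per group; the adjusted figures rest on the assumed correlation, equal group variances and a roughly linear relation. This is a low-cost improvement, not a fault that invalidates the outcome.

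**What to change.** - Have the reader of the postoperative scan, blinded to allocation, measure edema volume on the archived preoperative scan by the same method, and record the modality.
- State in advance that postoperative volume will be analysed with preoperative volume as a covariate (ANCOVA), on a transformed or rank scale if the volumes are skewed.
- Report the change from preoperative volume descriptively only, since as the tested outcome it is less efficient than adjustment.
- Flag patients whose only preoperative scan is CT, and repeat the analysis without them as a sensitivity analysis.
- Report the pre/post correlation and the residual SD, which a later trial will need.

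The cost is extra reading time on existing scans, with no new scan and no change in sample size. The remaining weakness is a noisier baseline for CT-only patients. If the full protocol already defines the preoperative size as a volume, the change reduces to recording the modality, handling CT-only patients and naming the covariate.

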Karnosky performance status, postoperative morbidity (cardiac arrythmia within 2 days after surgery, length of stay in the intensive care unit and in the hospital, surgical wound infection, pneumonia, readmission in the intensive care unit or in the hospital, surgical revision for postoperative intracerebral hematoma and/or life-threatening intracranial hypertension, coma, seizure, stroke, any permanent neurological deficit, any drug-related adverse event), and postoperative mortality are assessed on day 30 after surgery.

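### The arrhythmia item is counted only after surgery, although the allocated infusion is given at the start of the operation, so an arrhythmia confined to the operation is not counted under it

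*Protocol article*

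**What the plan says.** The protocol article gives the arrhythmia window twice. Section 3.8 defines it: "Postoperative morbidity includes cardiac arrythmia that occurs within 2 days after surgery". Section 3.5, listing what is assessed on day 30, has "postoperative morbidity (cardiac arrythmia within 2 days after surgery" as its first morbidity item. The parent secondary outcome in section 3.8 is "postoperative morbidity and mortality on day 30 after surgery".

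The exposure is timed in sections 3.5 and 3.7. The allocated treatment "is started at the time of skin incision and is administered over 15 to 20 minutes", and section 3.7 gives both arms the same start and duration.

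Three other provisions bear on intraoperative events:

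- Section 3.5 has blood pressure, heart rate, oximetry and "end-tidal carbon dioxide values from induction of anesthesia to discharge from the operating room" recorded. Rhythm events are not named, and section 3.8 does not make these values an outcome.
- Section 3.5 puts drug-related adverse events of any kind in its morbidity list. The list in section 3.8 does not have that item.
- Section 3.10 collects all serious adverse events, with no time limit stated, and sends them to the sponsor, pharmacovigilance and the independent safety board.

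**The concern.** The window for a safety item should include the time when the patient receives the drug. Here it opens only once surgery is over. The plan follows the biochemistry from the infusion onward, with pH, sodium, potassium and lactate measured at 30, 60 and 180 minutes and at 24 and 48 hours after it ends (section 3.9). The arrhythmia item does not share that starting point.

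Section 3.10 describes the lactate use as off-label, and the article's key points say that the pilot is meant to supply good data for designing further studies. An arrhythmia rate that leaves out the infusion and the rest of the operation is incomplete for that purpose, and a reader of the results table would not see this from the item's name alone.

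**Working it through.** **Time order.** Take skin incision as time 0. The infusion ends at 15 to 20 minutes. The operation goes on through opening of the dura, scoring of relaxation, any rescue step and tumor resection. The arrhythmia window opens when surgery ends and closes 2 days later. Overlap between infusion and window: none.

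**How events are classified under the text as written.**

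| Event | Arrhythmia item (3.5 and 3.8) | Drug-related item (3.5 only) | Serious event reporting (3.10) |
|---|---|---|---|
| During infusion or later in the operation, non-serious, not judged drug-related | no | no | no |
| Same timing, non-serious, judged drug-related | no | may count | no |
| Same timing, serious | no | only if judged drug-related | yes |
| 30 hours after surgery, any kind | yes | only if judged drug-related | only if serious |

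The first row is the gap. The second and third rows reach the trial by another route but are not counted as arrhythmia. An event that begins in theatre and continues after surgery could still be counted, so the point concerns events confined to the operation.

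**Can the size be found?** The article gives no arrhythmia rate, no duration of surgery and no timing of arrhythmia, so there is no figure of the plan to reproduce on this point. Two calculations on assumed inputs show how far any answer depends on the assumptions.

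1. Let r be the assumed risk of arrhythmia from infusion start to 2 days after surgery, and s the assumed share of affected patients whose arrhythmia is confined to the operation. Expected patients counted among the planned 25 per arm = 25 × r × (1 − s). Chance of counting at least one = 1 − (1 − r(1 − s))^25.
   - r = 10%: all events 25 × 0.10 = 2.5, chance 93%. With s = 25%, 50%, 75%, the count is 1.875, 1.25, 0.625 and the chance 86%, 72%, 47%.
   - r = 20%: all events 5, chance above 99%. With s = 25%, 50%, 75%, the count is 3.75, 2.5, 1.25 and the chance 98%, 93%, 72%.

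2. Assume that the excess risk due to the infusion is constant for 0.3 h and then decays with half-life h, with k = ln 2 / h, and that surgery ends S hours after incision. The share of such events falling before the end of surgery is [0.3 + (1 − exp(−k(S − 0.3)))/k] / [0.3 + (1 − exp(−k(48 + S − 0.3)))/k]. For S from 2 to 5 h this gives 75–97% at h = 1 h, 50–82% at 2 h, 29–58% at 4 h and 12–26% at 12 h.

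A range of 12% to 97% is not an estimate. It shows only that the share is above zero whenever some risk falls within the operation.

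**The case against.** The strongest reply is that an infusion-related arrhythmia is a drug-related adverse event, which section 3.5 already puts in the day-30 morbidity outcome, and that a serious one reaches the safety board whatever its timing. A postoperative window also fits an outcome named postoperative morbidity, and the 2-day limit matches the 48-hour sampling. The article is a condensed text, so recording of non-serious adverse events may be set out in the full protocol.

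Much of this stands. It rules out saying that intraoperative arrhythmias are not captured at all, or that non-serious events go unrecorded. It does not close the gap in the stated outcome. The drug-related route needs a causality judgement, possibly by staff who know the allocation, and it is missing from the definition in section 3.8. Neither route produces an arrhythmia count by arm for the exposure period. The window itself is not a detail left to another document, because the article states it twice.

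One could also read the 2 days as including the day of surgery. The postoperative label speaks against that reading, and if it is meant, the text should say so.

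**Conclusion.** The point holds as a worthwhile, inexpensive correction to one component of a secondary outcome. As worded, the arrhythmia item excludes the whole infusion and the rest of the operation. Non-serious intraoperative arrhythmias not attributed to the drug are left out of the by-arm count, and the rate passed to later trials omits the exposure period. This rests on the literal wording of sections 3.5, 3.7 and 3.8 and on no assumed rate. The size cannot be estimated from the documents. The primary outcome and the 25 patients per group in section 3.11 are unaffected.

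A reader might infer three stronger things that the documents do not support:

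- That most infusion-related arrhythmias are missed. This needs a duration of surgery and a time course of risk, and neither is given. Section 1 describes a water shift lasting several hours after lactate, so later events cannot be dismissed as unlikely.
- That the comparison is biased toward no difference. This would require the true rates to differ between arms, on which the article is silent.
- That the sampling times show the main biochemical change to be intraoperative. Section 3.9 says only that sampling serves to describe the effect, and it extends to 48 hours.

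**What to change.** In both section 3.5 and section 3.8, define the item as cardiac arrhythmia from the start of the allocated infusion to 2 days after surgery. Report events from infusion start to leaving the operating room separately from postoperative events, by arm. Reconcile the two morbidity lists on whether drug-related adverse events belong to the outcome.

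The cost is a line in each definition and a case-report-form item. Standard monitoring is already in place in theatre, so no procedure or patient is added. There are three downsides:

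- Arrhythmias due to anesthesia or surgery will be counted in both arms. Separate reporting makes this visible but does not remove it.
- Theatre staff who record the events may not be blinded. Section 3.6 names only patients and neurosurgeons as blinded and gives the allocation to the investigator, and the volumes in section 3.7 differ (2.5 versus 5 mL/kg). The report should state who recorded the events.
- Inclusions began in September 2020. For patients already treated, retrieval depends on what the anesthetic record shows, so the report should state for how many patients it could be done.
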